### Sample Size

An estimated 500 pediatric patients (18 years old or younger) will be recruited into the study. This sample size is informed by the previous VISION-D, VISION-MD, and VISION-Acute studies [17,21]. However, the sample size cannot be formally calculated because it depends on the incremental improvement in the performance of the app achieved through machine learning using the training data generated early in the study. The split between training and testing data will be determined during the study according to the quality of the data collected. The study management team monitors the progress of data collection and accuracy and updates the study teams weekly. The study will continue until the accuracy of the app for measuring VS in pediatric patients is sufficient for various clinical use cases.

In addition, recruitment targets according to age, sex, Fitzpatrick skin tone, and medical history have been defined, as shown in Table 3, to ensure accuracy in a broad range of clinically relevant patients.

**Table 3 table3:** Demographic and medical history recruitment targets.

	Targets
Age	≥12% aged 0-1, 1-2, 2-5, 5-11, 11-14, 14-18 years
Sex	≥40% male; ≥40% female
Skin tone	15% of participants will have Fitzpatrick skin tones 4, 5, or 6 (this is not a hard target as achieving this figure depends on the demographic diversity of the study region)
Medical history	≥40% in each of the following categories: Febrile (≥38 °C) Afebrile Ill (as judged by the clinical staff); to ensure a spread of conditions, no more than 50% of recruited patients will have an acute respiratory illness (eg, bronchiolitis, asthma, virus-induced wheeze, pneumonia, and croup) Well, including pediatric patients with a minor injury

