**Methods:**

The study is recruiting pediatric patients (younger than 18 years of age) attending the Sunderland Royal Hospital pediatric emergency department of the South Tyneside and Sunderland National Health Service Foundation Trust. High-resolution videos of the face (and torso in children younger than 5 years of age) and audio recordings (to explore the value of crying, wheezing, coughing, and other sounds in predicting illness) are made using the Lifelight Data Collect app. VS are measured simultaneously using SOC methods (finger clip sensor for PR and oxygen saturation; manual counting of RR). Feedback from patients, parents, carers, and nurses who use Lifelight is collected via questionnaires. Anticipated recruitment is 500 participants, with subtargets for age, sex, and skin tone distribution (Fitzpatrick 6-point scale). Early data will be used to refine the algorithms. A separate dataset will be retained to test the performance of the app against predefined targets.

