The VISION-Junior study explores the measurement of VS using a Lifelight app developed for pediatric patients (aged 18 years or younger) attending the pediatric emergency department. As in VISION-MD in adults, high-resolution full-face videos will be recorded. In younger children (younger than 5 years of age), the video will also include the torso to increase the surface area from which the signal is recorded, and because the torso is likely to move less than the face. Audio data will also be recorded, as crying, wheezing, coughing, and other sounds can also predict illness in children [22,23].

The aim of the VISION-Junior study is to assess whether the app can be used to accurately measure VS in pediatric patients. This protocol describes the collection of data that will initially be used to develop the algorithms for the measurement of VS in children. Later data will be used to assess the accuracy of the app across the range of VS values encountered in children of different ages. The objectives are as follows.

The primary objective is to collect data to support the development of the app for the accurate measurement of PR, RR, and oxygen saturation in pediatric patients and to assess the accuracy of measurements against SOC methods. Secondary objectives are: (1) to assess—using the collected PPG data—whether other (direct or indirect) measurements can be made using the app, including temperature, BP, PR variability, and audio analysis; (2) to evaluate the impact of subject-specific variables on the PPG VS measurements (eg, medication, cosmetics, facial or body hair, and skin tone); (3) to obtain data to understand patient and parent or guardian or carer habits and preferences for VS measurement using questionnaires (Multimedia Appendices 1 and 2); and (4) to assess the usability of Lifelight Junior for measuring VS in pediatric patients through questionnaires completed by participating health care professionals (Multimedia Appendix 3).

Most of the data collected in the study will be used to train the app algorithms to measure VS in pediatric patients. The remaining data will be kept separate and used to assess the accuracy of the algorithms at regular intervals during the data collection period. The study delivery process will be responsive to this learning curve to increase the likelihood that the predetermined accuracy target for each VS estimation is achieved by the study end.

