## Results

The study started on June 12, 2023, and as of December 20, 2023, had recruited 303 participants. The study was extended until the end of March 2024 to enable the target recruitment (500) to be met; 532 participants had been recruited as of April 5, 2024.

Data are currently being used for machine learning to refine the algorithms to improve clinical accuracy. We anticipate that final analyses to determine the performance of the app against the targets set out in Table 2 will be complete by mid-August 2024. The performance of the app will be determined across the range of VS values encountered in children in clinical practice by comparing the VS values recorded using PPG versus standard methods.

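### The train/test split may be set during the study according to data quality, and no test-set size or cut-off is fixed, so the test set can end up cleaner than the population and its precision is left open

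*Protocol article*

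**What the plan says.** Protocol article, Sample Size: "The split between training and testing data will be determined during the study according to the quality of the data collected". The same paragraph gives the total, "An estimated 500 pediatric patients (18 years old or younger) will be recruited into the study", and explains why it has no formal basis: "the sample size cannot be formally calculated because it depends on the incremental improvement in the performance of the app".

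Other sections bear on the split:
- Abstract, Methods: "Early data will be used to refine the algorithms", with a separate dataset retained for testing.
- Introduction: "Most of the data collected in the study will be used to train the app algorithms to measure VS in pediatric patients". The remainder is kept apart and used to check accuracy at regular intervals while data are still being collected.
- Introduction, on order: "Later data will be used to assess the accuracy of the app across the range of VS values encountered".
- Results: "532 participants had been recruited as of April 5, 2024", and the data are already in use for machine learning.

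Table 2 sets the pulse-rate target at an RMSE of no more than 5 beats per minute. No section states how many children the test set will hold, where the cut-off falls, or how children are allocated to it.

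**The concern.** The retained test set decides whether the Table 2 targets are met, and assessing accuracy against standard of care is part of the primary objective. A rule that lets observed data quality shape that set is risky because quality is linked to the error being measured. The Limitations section names excessive movement and insufficient light as threats to signal quality. Study Procedures has staff record movement, anything obscuring the face, and whether the app lost the face. If such information affects where the split falls, or which recordings are tested, the test set can hold fewer difficult recordings than clinical use will produce. Later analysis of that set alone cannot reliably undo this.

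The second issue is precision. The article treats sample size as incalculable because it depends on how the algorithm learns. That is a fair reason for not calculating a training size. It does not apply to the test set: once the algorithm is locked, the precision of its RMSE for a given number of children can be stated under an assumed error distribution.

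**Working it through.** **The plan's own figure.** The total of about 500 (532 recruited) covers training and test data together. It cannot be reproduced, because the article says it was not formally calculated and gives no SD, power or target precision. The only bound on the test share is that most data go to training, so it is below half: under 250 of 500, or under 266 of 532.

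**Step 1: how the quality mix can move the pulse-rate RMSE.** The article gives no error SD and no rate of poor recordings, so every input here is an assumption. With zero-mean errors and a proportion p of poor recordings:

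RMSE = √[(1 − p) × SD_good² + p × SD_poor²]

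For SDs of 4 and 9:
- p = 20%: √(0.80 × 16 + 0.20 × 81) = √29.0 = 5.39, which misses the target.
- p = 5%: √(0.95 × 16 + 0.05 × 81) = √19.25 = 4.39, which meets it.

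The same formula over a range of assumed SDs:

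| SD good / poor | RMSE, 20% poor | RMSE, 5% poor | Verdict against 5 |
|---|---|---|---|
| 3 / 7 | 4.12 | 3.32 | meets both times |
| 4 / 7 | 4.75 | 4.20 | meets both times |
| 3 / 9 | 4.84 | 3.55 | meets both times |
| 4 / 9 | 5.39 | 4.39 | changes |
| 5 / 9 | 6.02 | 5.27 | misses both times |

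A cleaner test set lowers the RMSE in every row, by 0.55 (4.75 − 4.20) to 1.29 (4.84 − 3.55) beats per minute. The pass/fail verdict changes only where the true value lies not far above the limit.

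**Step 2: precision of an observed RMSE of 5.0.** Assume one reading per child and independent, zero-mean normal errors. The 95% limits are 5.0 × √(n/χ²), using the 97.5% and 2.5% points of chi-square with n degrees of freedom:

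| Test n | Share | χ² points | 95% CI |
|---|---|---|---|
| 50 | 10% of 500 | 71.42, 32.36 | 4.18 to 6.22 |
| 100 | 20% of 500 | 129.56, 74.22 | 4.39 to 5.80 |
| 160 | 30% of 532 | 196.92, 126.87 | 4.51 to 5.62 |

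**Step 3: how far to trust those intervals.** A mixture of good and poor recordings is heavy-tailed. Under the 80/20 mixture with SDs 4 and 9, simulation (40,000 runs) shows the nominal 95% chi-square interval covering the true RMSE only about 82% of the time at n=130 and n=160. The standard error is about 1.47 times the normal-theory value. At n=160 the normal-theory half-width is (5.62 − 4.51)/2 = 0.56; scaled by 1.47 it is about 0.8. Repeat readings from one child, which Study Procedures makes possible, would widen the interval further.

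**The case against.** The strongest reply is that the sentence is about proportion, not selection. It stands in the Sample Size section, straight after the text on how training drives the total, and can be read as saying only how much data goes each way. If testing then uses later data, as the Introduction says, no one is choosing clean recordings for the test set. This stands as a limit on the claim. A reader might infer that recordings are to be assigned to the test set by quality; the article does not say so. The reply does not remove the problem, because a cut-off moved in response to observed quality still lets quality shape the test set.

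A reader might also infer that the sentence contradicts the early/late order in the Abstract and Introduction. It need not: a time split whose cut-off depends on how much usable early data accrues would satisfy all three passages. They are unreconciled, not contradictory.

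It can also be said that poor recordings are limited elsewhere: children who move excessively are excluded, up to three attempts are allowed, and problematic readings are dropped. That is true, but it concerns which readings enter any analysis. It does not make the split blind to quality.

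Finally, an article commonly leaves the exact fraction and method to the full protocol or analysis plan. Silence alone would not be a finding. Here the article positively states a data-dependent rule, which a later document could not make quality-blind without departing from it.

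**Conclusion.** The concern holds in a limited form. The plan permits observed data quality to influence the split and fixes neither a test-set size nor a cut-off, so the Table 2 result can be optimistic and its precision is unknown in advance. Whether bias will occur, and how large it would be, cannot be established from the article. The move from 5.39 to 4.39 rests on assumed SDs of 4 and 9 and an assumed fall from 20% to 5% poor recordings; four of the five SD pairs tried leave the verdict as it was.

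The statement that sample size cannot be calculated is sound for training and too broad for testing. It would be equally too broad to say that test precision depends on n alone: it also depends on the error distribution and on clustering within child. The intervals of about 4.2 to 6.2 (n=50), 4.4 to 5.8 (n=100) and 4.5 to 5.6 (n=160) are therefore best-case widths. Nor do these figures show that the study is too small, since the test-set size is not stated.

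**What to change.** Replace the Sample Size sentence with a rule that locks the test set by participant, with all recordings of a child on one side, and blind to recording quality and app error. Two forms would serve:
- a random draw stratified on the Table 3 variables; or
- a fixed calendar cut-off, which agrees with the Introduction's use of later data for accuracy.

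Under either form, only children whose recordings have not been used in training or in the interim accuracy checks should be eligible. The Results section says machine learning is already under way, so a random draw from all 532 could place training children in the test set.

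Fix the test-set size in advance. Limit the statement on sample size to training, and add the expected CI width for the chosen test n under stated error assumptions, including a heavy-tailed case. Report the RMSE with a bootstrap CI that resamples participants.

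The cost is wording, a scripted allocation, and a fixed share of the data withheld from training. No further recruitment is needed. If too few unused children remain, the models must be retrained without the test children, which is the main expense and a reason to settle the rule before the final analysis.

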### Data Analysis

All statistical analyses will be performed using Python (Python Software Foundation). Training data will be used for machine learning to improve the performance of Lifelight Junior for measuring VS in pediatric patients. Appropriate machine learning models will be developed according to the data collected. This is likely to include signal processing and measurement algorithms for PR and RR, and multilayer neural network-based approaches for BP, similar to those used in the adult version of the app.

The separate set of test data will subsequently be used to determine the performance of the app for measuring VS in pediatric patients. Correspondence between VS measurements predicted by the app and the measurements taken manually using SOC methods will be compared using regression coefficients, mean error, and SD, and compared against the performance targets set out in Table 2. An accuracy target will be considered met if the mean error and SD for the app measurements are at least equal to the target (Table 2). Heat maps or scatter plots will also be developed.

Linear regression will be used to assess the impact of skin tone on the accuracy of the app for measuring each VS, using the Fitzpatrick skin tones as the explanatory variable.

Quantitative data from the questionnaires will be summarized. Thematic analysis will be used to analyze free-text responses to identify perceptions of the app and variations in the way patients, their parents or carers, and health care professionals interact with it and any challenges they encounter.

All analyses will be completed per protocol since there is no intention to treat. There will be no imputation of missing or implausible data, and any missing, implausible, or problematic readings will be excluded from analysis.

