### Performance Targets

While Lifelight is certified as a class I CE medical device [18], the performance of Lifelight Junior needs to be appropriate for routine clinical practice in pediatric patients. Table 2 lists the performance targets for Lifelight Junior for measuring VS in pediatric patients; training data collected during VISION-Junior will support progress toward these targets.

**Table 2 table2:** Performance targets in VISION-Junior.

Vital sign	Performance target	Reference
Pulse rate	Root mean square error ≤5 beats per minute	[25]
Respiratory rate	Maximum error of 5 breaths per minute for 100% of measurements	Minimum standard met by all approved respiratory monitors
Oxygen saturation	Maximum error tolerance 4%	[26]

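### The pass rule compares mean error and SD with Table 2 limits that are RMSE and maximum-error limits, so an app can be declared to meet a target that it breaches, most seriously for respiratory rate.

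*Protocol article*

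**What the plan says.** The targets are in the protocol article under Performance Targets, Table 2:

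- Pulse rate: "Root mean square error ≤5 beats per minute".
- Respiratory rate: "Maximum error of 5 breaths per minute for 100% of measurements".
- Oxygen saturation: "Maximum error tolerance 4" per cent, with no statement of the share of readings that it covers.

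The comparison is described under Data Analysis. App and standard-of-care values "will be compared using regression coefficients, mean error, and SD, and compared against the performance targets set out in Table 2". The decision rule follows: "An accuracy target will be considered met if the mean error and SD for the app measurements are at least equal to the target", with a pointer to Table 2.

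The article does not call for RMSE or the largest error to be computed, and it does not convert Table 2 into limits on mean error and SD. The size of the test set is open: "The split between training and testing data will be determined during the study according to the quality of the data collected".

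**The concern.** The rule tests statistics that the targets do not limit. Mean error and SD describe the centre and spread of the errors. RMSE combines the two, and a maximum-error limit concerns the extremes. Keeping the centre and spread within 5 does not keep the combination within 5, and it says little about whether every reading is within 5. The direction of the comparison is also loosely worded for an error limit, where smaller is better.

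This is the only pass criterion the article states for accuracy, and accuracy against standard of care is part of the primary objective. The Results section says that the final analyses will determine performance against Table 2. A wrong declaration that a target is met would be an error in the main result. The article prints both the targets and the rule, so this is a conflict within the stated text and not a detail left to an analysis plan.

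**Working it through.** **Inputs.** Limits L from Table 2: 5 beats per minute (RMSE), 5 breaths per minute (maximum error, all readings) and 4% (maximum error). There is no power or sample size figure to reproduce, because the article says that "the sample size cannot be formally calculated".

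**Assumptions.**
- The rule is read as |m| ≤ L and s ≤ L, where m is the mean error and s the SD, and the loose comparison is taken as no worse than.
- Errors are normal wherever a share of readings is given.
- Readings are independent wherever all n readings are considered.
- Test-set size n is 50 to 250. The Introduction gives most of the data to training, so 250 (half of 500) is near the upper end at one reading per child.

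**1. Respiratory rate.** The share of errors outside the limit is P = 1 − [Φ((L − m)/s) − Φ((−L − m)/s)].

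- m = 0, s = 5: P = 1 − [Φ(1) − Φ(−1)] = 0.317. The rule passes; Table 2 allows 0.
- m = 5, s = 5: P = 1 − [Φ(0) − Φ(−2)] = 0.523. The rule still passes.
- m = 4, s = 4, well inside the rule: P = 1 − [Φ(0.25) − Φ(−2.25)] = 0.414.

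The chance that all n readings comply is (1 − P)^n. With m = 0, s = 5 and n = 100 it is about 3 × 10⁻¹⁷.

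For an unbiased app to have a 95% chance that all n readings comply, the SD can be at most L/z, where z is the normal quantile at (1 + 0.95^(1/n))/2:

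| n | Largest SD, L = 5 | Largest SD, L = 4 |
|---|---|---|
| 50 | 1.52 | 1.22 |
| 100 | 1.44 | 1.15 |
| 150 | 1.40 | 1.12 |
| 250 | 1.35 | 1.08 |

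The rule allows SD 5, which is 5/1.52 = 3.3 to 5/1.35 = 3.7 times as large.

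**2. Oxygen saturation**, if the tolerance means the largest single absolute error. The formula depends only on m/L and s/L, so the shares are the same: m = 0, s = 4 passes with 31.7% of errors above 4, and m = s = 3.2 passes with 41.4%. The last column of the table gives the SD needed.

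**3. Pulse rate.** RMSE² = m² + s² (SD with divisor n). This needs no distributional assumption.

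- m = 0, s = 5: RMSE = 5.00. The target is met, so the pass is correct.
- m = 4, s = 4: RMSE = √32 = 5.66. The rule passes and the target is breached.
- m = 5, s = 5: RMSE = √50 = 7.07, 41% above the limit. This is the largest RMSE that the rule can pass.

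**4. Not only at the edge.** In 20,000 simulated test sets per size, with true mean and SD both 0.8 × L, the rule passed while RMSE exceeded its limit in 85.5% (n = 50), 96.5% (n = 100) and 99.9% (n = 250). It passed while the largest error exceeded its limit in 95.4%, 99.3% and 100.0%.

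**5. Alternative reading, |m| + s ≤ L.** Then RMSE² = m² + s² ≤ (|m| + s)² ≤ L², so pulse rate cannot pass wrongly. The maximum-error targets still can. On the boundary |m| + s = L, the share outside the limit is 31.7% at m = 0, 20.6% at m = 0.25L and 16.0% at m = 0.5L.

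**The case against.** A reader might infer that any app breaching Table 2 would be declared compliant, or that the rule gives a false pass for all three vital signs. The documents do not support that. An unbiased pulse rate app passes only with SD ≤5, which is RMSE ≤5, and any app with RMSE above 7.07 fails. Some apps breach all three targets and pass all three (for example mean and SD both 4, 4 and 3.2), but this shows what can happen, not what must.

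Nor is the rule lax by a known factor. With no mean-error or SD limits in Table 2, it is strictly undefined, and the figures depend on a reading that the article does not state. Under the sum reading the pulse rate problem disappears. This stands, but respiratory rate fails under both readings.

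The oxygen saturation row does not say that it covers all measurements, and its cited source is not available here. That finding is therefore conditional.

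The loose comparison most naturally means at least as good as, and the calculations use that sense, so its direction is a drafting matter only.

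Finally, Table 2 remains the declared yardstick, and RMSE can be derived from reported mean error and SD. That helps pulse rate only, since a largest error cannot be recovered from a mean and an SD. The data-collection app shows no estimates and is not used clinically, so no participant's care depends on the rule. The reported conclusion on accuracy does.

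**Conclusion.** The concern holds in this form: the stated pass rule and the stated targets use different metrics, and the rule can declare a target met when it is breached. The mismatch needs no assumption; its size does.

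- **Respiratory rate:** the serious case. About 32% of errors can lie outside a limit that allows none, with zero bias, normal errors and separate limits on mean and SD.
- **Oxygen saturation:** the same size, provided the tolerance means the largest single absolute error.
- **Pulse rate:** a wrong pass needs bias, is capped at RMSE 7.07 against 5, and vanishes under the sum reading.

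The SDs needed for all readings to comply also rest on independence and on assumed test-set sizes. This should be corrected before the test data are analysed, because it decides the main accuracy result and the correction needs only wording.

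**What to change.** Replace the pass sentence under Data Analysis with:

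> A target is met when the statistic named in Table 2, computed on the test data not used for training, satisfies its limit: pulse rate, RMSE ≤5 beats per minute; respiratory rate, 100% of absolute errors ≤5 breaths per minute; oxygen saturation, largest absolute error ≤4 percentage points.

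If the 4% tolerance for oxygen saturation means something else, state that in Table 2 and make the last clause match.

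Report a 95% confidence interval for the RMSE and for the share of readings within the limit. An interval for the sample maximum is not advised: the maximum grows with test-set size, and ordinary intervals do not suit it. Keep mean error, SD and regression coefficients as descriptive results.

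The cost is analysis wording only, with no new data. The downside is a stricter rule, under which results may look less favourable. The two maximum-error targets also become harder to meet as the test set grows, so the number of test readings should be reported beside each verdict.
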